|                | 
In case intra-operative volume requirements exceed the amount of bottles of Investigational Product supplied by the pharmacy in a blinded manner then open-label treatment with a balanced crystalloid solution (Sterofundin ISO) will be performed during surgery (also using oesophageal Doppler measurements for deciding on the administration of the fluids).
 
All Investigational Products will be administered in a blinded manner. Blinding will be performed by the pharmacy who will compile the appropriate amount of bottles and label with sequential numbers.
 
Two independent anaesthetists will be involved to maintain blindness: one for maintenance of anaesthesia, one for Doppler measurements and volume and haemodynamic therapy.
 
Treatment Duration
 
Treatment with Investigational Product starts after reliable basal oesophageal Doppler measurements are obtained and before skin incision.
 
After final positioning of the patient in the operating theatre the oesophageal probe will be placed and basal measurements will be recorded after correct placement of probe and reliable measures are obtained. Thereafter, before skin incision, the first bolus of Investigational Product of 250 ml/5 min will be given and the algorithm of the individualized volume replacement therapy is initiated. Oesophageal Doppler guided volume replacement will be performed throughout surgery.
 
Treatment with Investigational Product ends with surgery when the oesophageal probe is withdrawn. In case all bottles of Investigational Product as compiled by the pharmacist are used up before end of surgery then open-label treatment with a balanced crystalloid (Sterofundin ISO) will be performed from then on during surgery.
 
After surgery, on ICU, volume replacement will be performed at the discretion of the attending physician. In case colloidal volume replacement is required on ICU on the day of surgery no HES-product but other colloidal volume replacement (e. g. gelatine) will be used. All volume/fluid replacement therapy will be recorded (separately for colloids and crystalloids).
 
Trigger for transfusion of erythrocyte concentrate (EC) is an haematocrit of < 25% (or if necessary). Infusion of fresh frozen plasma (FFP) will aim at a proportion of EC:FFP=2:1 and 1:1 after 4 infusions of EC respectively. Trigger for infusion of platelet concentrate (PC) is a thrombocyte count of < 50.000/<math>\mu</math>l.
 |

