### **10.2.3 Duration of treatment**

Treatment with Investigational Product starts after reliable basal oesophageal Doppler measurements are obtained and before skin incision.

After final positioning of the patient in the operating theatre the oesophageal probe will be placed and basal measurements will be recorded after correct placement of probe and reliable measures are obtained. Thereafter, before skin incision, the first bolus of Investigational Product of 250 ml/5 min will be given and the algorithm of the individualized volume replacement therapy is initiated. Oesophageal Doppler guided volume replacement will be performed throughout surgery.

Treatment with Investigational Product ends with surgery when the oesophageal probe is withdrawn. In case all bottles of Investigational Product as compiled by the pharmacist are used up before end of surgery then open-label treatment (in addition to basal balanced crystalloid infusion) with a balanced crystalloid (Sterofundin ISO) will be performed from then on during surgery.

After surgery, on ICU, volume replacement will be performed at the discretion of the attending physician. In case colloidal volume replacement is required on ICU on the day of surgery no HES-product but other colloidal volume replacement (e. g. gelatine) will be used. All volume/fluid replacement therapy will be recorded (separately for colloids and crystalloids).

(Note: The loading of the epidural catheter and start of continuous epidural analgesia will be performed at the end of surgery after all intraoperative, study-related measurements have been finalized.)

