### **Post-operative patient management**

A standardised therapy management with respect to enteral nutrition, mobilisation etc will be applied and documented in detail in the CRF.

On ICU volume replacement will be performed at the discretion of the attending physician. See “unauthorised concomitant medication”.

For the assessment of the second primary variable, time until fully on oral diet, it has to be assessed for a period of maximally 15 days. It will be assessed for each day (on the subsequent day) whether the patient receives parenteral nutrition. As soon as the patient is off parenteral nutrition and has taken nutrients via oral (not enteral) pathway at least three times that day no further recording of nutritional diet is required.

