### **Unauthorised concomitant medication:**

Aside from basal fluid administration no other colloid or crystalloid volume replacement agents than study medications will be applied *during surgery* as long as Investigational Product as compiled by the pharmacist is available, with the exception of concentrated electrolytes for individual corrections.

On ICU if volume replacement with colloidal is required on the day of surgery no HES-product but other colloidal solutions (e. g. gelatine) will be used.

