## \* laboratory measurements in blood/serum sample:

- arterial blood gas analysis/acid base status/electrolytes. Blood sampling for BGA should be performed as close as possible to the time, at which the corresponding hemodynamic measurement is done.
- haemostasis/coagulation parameters (PT, aPTT, Fibrinogen, FVIII:c, vWF-Ag, vWF-RiCo; CT, CFT, MCF using ExTEM und FibTEM)
- cardiac function (Troponin or high-sensitivity Troponin, NT-Pro-BNP)
- inflammatory reaction parameters (facultative: IL-6, IL-10)

**day 0/** intensive care unit (ICU) –

- Aldrete Score (*on admission*)
- Haemodynamics (SAP, DAP, MAP, HR, CVP (on admission and 6hourly); PiCCO: CI, SV, SVR, ITBVI, EVLWI) (on admission and after 6 hours)
- blood gas analysis (arterial or venous blood sample) including acid base status and electrolytes: (on admission, 6 hours after admission). Blood sampling for BGA should be performed as close as possible to the time, at which the corresponding hemodynamic measurement is done.
- abdominal pressure (*6 hours after admission*)
- Ventilatory support as requested to maintain normocapnia and oxygen saturation (PCV, CPAP)
- Concomitant medication, infusion therapy (separate for colloids (i. e. gelatine) crystalloids, blood products)
- Diuresis (sampling period until next morning about 6 o'clock)
- Adverse events and adverse reactions

- check of discharge criteria

**day +1** (1st post-operative day)/ On ICU: Postoperative care will follow a standardised regimen.

- Haemodynamics (SAP, DAP, MAP, HR, CVP(every 6 hours)); PiCCO: CI, SV, SVR, ITBVI, EVLWI (every 12 hours/ in the morning and in the evening)
- abdominal pressure (in the morning)
- Ventilatory support (PCV, CPAP) as requested to maintain normocapnia and oxygen saturation
- Blood sampling for laboratory evaluation\*, urine sample for laboratory evaluation\*\*
- Aldrete Score (in the morning)
- SIRS-criteria
- Nursing Delirium Screening Scale (NuDesc) (three times daily)
- Injury scores (APACHE II, SAPS II, SOFA)
- Assessment of “fit for discharge” criteria (once on ICU - preferably in the morning)
- Concomitant medication including parenteral nutrition, infusion therapy (separate for colloids i. e. gelatine and crystalloid, blood products)
- Diuresis (Sampling period is from morning until next morning about 6 o'clock)
- PONV
- body weight (if possible)

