- Gastrointestinal parameters (bowel movement on auscultation, time to full oral nutrition, time to first defaecation, time to first flatus)
- Adverse events and adverse reactions
- Check of discharge criteria

\* laboratory measurements in blood/serum samples 1st post-operative day:

- in the morning sample: Troponin or high-sensitivity Troponin, NT-Pro-BNP, IL6 (facultative), IL10 (facultative), PCT, CRP, WBC, creatinine, BUN, PT, aPTT, vWF-Ag, vWF-CoRi, ROTEM
- every 6 hours: blood gas analysis/acid base status/electrolytes (arterial or venous blood sample). Blood sampling for BGA should be performed as close as possible to the time, at which the corresponding hemodynamic measurement is done.
- additional for injury scores: bilirubin, thrombocytes, haematocrit

\*\*\*laboratory measurements in urine sample: creatinine,  $\alpha$ 1-MG,  $\beta$ -NAG

**day +2 – +n**, until fulfillment of “fit for discharge”-criteria (Marshall, Chung 1997, 1999) however not longer than day +5 (including day +5) (*blood sampling also on postoperative day +3 and +7*)

- Haemodynamics (SAP, DAP, MAP, HR, CVP(every 6 hours); PiCCO: CI, SV, SVR; ITBVI, EVLWI (every 12 hours))
- Ventilatory support (PCV, CPAP) as requested to maintain normocapnia and oxygen saturation
- Blood sampling/urine sampling for laboratory evaluation (daily)\*
- SIRS-criteria
- NuDesc (3x daily)
- Injury scores (APACHE II, SAPS II, SOFA) (once daily)

- Concomitant medication, infusion therapy (separate for colloid (gelatine) and crystalloid, blood products)
- Diuresis (sampling period from morning until next morning about 6 o'clock)
- PONV
- Surgical complications (e.g. anastomotic insufficiency, intestinal leakage, wound healing)
- Gastrointestinal parameters (bowel movement on auscultation, start of enteral nutrition, time to first defaecation)
- Mobilisation
- "Fit for discharge"-criteria (Marshall, Chung, 1997, 1999) (once on ICU-preferably in the morning)
- Aldrete Score (assessment at time when discharge from ICU)
- Adverse events and adverse reactions
- check of discharge criteria

\*laboratory measurements on ICU

- once daily on ICU (maximally until day 5 (including day 5): renal function parameters (blood/serum: creatinine, BUN; urine: creatinine,  $\alpha$ 1-MG,  $\beta$ -NAG), WBC
- additional for injury scores: arterial pH, haematocrit, Sodium, Potassium, HCO3, bilirubin, platelets
- postoperative days 3 and 7: creatinine in serum

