20= serum creatinine

**\*Time n usually (if not otherwise mentioned) is defined as time when patient ready for discharge (exception of nutrition control) maximally until postoperative day 5 (including POD 5)**

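### HES on ICU is barred only on the day of surgery, so nothing keeps it out of any arm, including the crystalloid control, from day +1, although the schedule names gelatine as the colloid to day +5

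*Protocol*

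**What the plan says.** The restriction appears in three places, and each limits it to the ICU and to the day of surgery.

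- Section 11, Unauthorised concomitant medication: "On ICU if volume replacement with colloidal is required on the day of surgery no HES-product but other colloidal solutions" are to be used.
- Synopsis, Treatment Duration: "In case colloidal volume replacement is required on ICU on the day of surgery no HES-product but other colloidal volume replacement" is to be used. Section 10.2.3 repeats this sentence.

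Outside that window the choice is free. Section 10.2.3 states: "After surgery, on ICU, volume replacement will be performed at the discretion of the attending physician". Section 11, Post-operative patient management, says the same ("On ICU volume replacement will be performed at the discretion of the attending physician") and refers only to the unauthorised-medication paragraph for limits.

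The visit schedule in section 14.1 describes the fluids to be recorded. The day +1 line reads "infusion therapy (separate for colloids i. e. gelatine and crystalloid, blood products". The line for day +2 onward reads "infusion therapy (separate for colloid (gelatine) and crystalloid, blood products", and that period runs "however not longer than day +5 (including day +5". The Synopsis visit schedule uses similar wording.

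**The concern.** A rule that lapses at the end of day 0 does not fit a schedule that assumes gelatine is the colloid up to day +5. Either HES was meant to be avoided for that whole period and the rule is too short, or HES was acceptable from day +1 and the recording lines name only one of the possible colloids. A site cannot tell which from the text.

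At stake is the purpose of the third arm. Section 7.2 lists renal function and adverse events among the secondary objectives and plans a descriptive comparison of the two HES strategies with crystalloid alone. If control patients receive HES from day +1, later renal samples and later adverse events in that arm may partly reflect HES, and the contrast would shrink. An analysis plan cannot undo such exposure, so the matter belongs in the protocol.

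**Working it through.** No power, alpha or effect size is involved. The check sets the time limits side by side and counts what falls after the bar ends.

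**Inputs**
- HES bar: ICU, day 0 only, no arm singled out (Synopsis; sections 10.2.3 and 11).
- Renal sampling: POD 1 morning; then daily on ICU to POD 5 at most (serum creatinine, BUN, urine markers); serum creatinine also on POD 3 and POD 7 in the morning (sections 12.2 and 14.1).
- Adverse events: from the start of study product to POD 5 (section 12.2).
- Coagulation: last sample on POD 1 morning (section 12.2).

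**Step 1: is HES barred anywhere after day 0?** No. The three statements agree with each other, and the only cross-reference on limits leads back to the day-0 rule. HES from day +1 is thus open because no clause forbids it and ICU fluids are left to the doctor. It does not follow from the gelatine lines, which are recording instructions and, if anything, point the other way.

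**Step 2: which samples come after at least one full unrestricted day (POD 1)?** These are the samples from POD 2 on. For a patient in hospital to POD 7, and without counting the extra sample at discharge:
- Serum creatinine, minimum (off ICU by POD 2): POD 3 and 7 = 2 samples.
- Serum creatinine, maximum (on ICU to POD 5): POD 2, 3, 4, 5 and 7 = 5 samples.
- BUN and urine markers, taken on ICU only: from 0 (off ICU by POD 2) to POD 2, 3, 4 and 5 = 4 samples.

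**Step 3: how much of the adverse event window lies after the bar?** Day 0 to POD 5 is 6 calendar days; 6 − 1 = 5 of them follow day 0.

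**Step 4: what is largely protected?** The POD 1 morning renal sample and all coagulation results, because little time passes between the end of day 0 and that morning.

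**Step 5: how far does scheduled fluid recording reach?** The day +2 to +n period ends at POD 5 at the latest, and the footnote to section 14.2 agrees: the end point "is defined as time when patient ready for discharge (exception of nutrition control) maximally until postoperative day 5 (including POD 5". The last creatinine is on POD 7, and 7 − 5 = 2 calendar days later. By the schedule alone, POD 6 and the hours before the POD 7 sample are not covered. Against this, section 10.2.3 has all volume replacement recorded and sets no end date. It asks for a split into colloids and crystalloids, not by product.

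**The case against.** The strongest defence is that the day-0 limit is deliberate. Section 9.5 caps HES per day (50 ml/kg for the 6% solution, 30 ml/kg for the 10% solution). A patient may have used much of that allowance in theatre, and staff blinded to the arm cannot know how much is left. A bar for the rest of that day fits the cap exactly. This is plausible, but the Protocol does not give it as the reason, and a dose-safety purpose would not protect the later renal comparison.

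The second defence is that the intervention is intraoperative. Control patients may already receive gelatine on ICU on day 0, so crystalloid alone can only describe treatment during surgery, and free post-operative care is a legitimate choice in a phase IV trial of registered products. This stands in part: the control arm was never meant to be colloid-free on ICU. But gelatine in the control arm is not the same as the substance whose safety is being compared.

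It is also true that the gelatine parenthesis appears on the day 0 ICU line too, so it may simply be repeated wording, and that the exposed comparison is descriptive, with exploratory p-values under section 16.2.

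Three stronger readings are tempting and not supported. A reader might infer that the rule and the schedule contradict each other; they do not, since recording lines are not rules. A reader might take the sample and day counts as a measure of contamination; they measure only the opportunity for it. A reader might infer that post-operative HES would be untraceable; section 10.2.3 has all volume replacement recorded, and the case report form, which is not shown, may capture the product.

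**Conclusion.** The point holds as a minor design weakness. The Protocol leaves HES open from day +1 in every arm, including the control, while its own schedule treats gelatine as the colloid to day +5. HES given to control patients could dilute the descriptive HES-versus-crystalloid comparison in the renal samples from POD 2 on and in most of the adverse event window.

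The size of any dilution cannot be estimated, because the Protocol gives no rate of post-operative HES use; if no control patient received it, there would be none. The creatinine count assumes a stay to POD 7. The first primary endpoint is measured during surgery and cannot be affected. A reader might suspect an effect on the second, time to full oral diet, but nothing in the Protocol supports a claim about it.

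**What to change.** In the Synopsis (Treatment Duration), section 10.2.3 and section 11 (Unauthorised concomitant medication), extend the no-HES rule through POD 5, on ICU and on the ward, in all arms. This brings the rule into line with the schedule's gelatine wording. Other colloids stay available.

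Record any HES given despite the rule, by product and day, up to the POD 7 creatinine, and tabulate it by arm beside the renal results. This also covers POD 6 and the hours before the POD 7 sample, which the extended bar would not reach.

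The cost is less freedom in post-operative colloid choice, one extra recorded item and one table. No visits, samples or patients are added. If the sponsor does intend HES to be allowed from day +1, the Protocol should say so, the gelatine wording should be corrected, and the product-level recording and table are still needed.

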## **12 DEFINITION OF THE PRIMARY AND SECONDARY VARIABLES**

### **12.1 Primary Variable**

First primary endpoint: Intraoperatively required amount of HES (mLs) under target controlled volume replacement therapy.

Second primary endpoint: Time until fully on oral (solid) diet (days): Fully on oral (solid) diet is reached when no more parenteral and enteral nutrition is given and the patient has taken nutrients via the oral pathway for at least three times that day.

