| Primary Variable     | 
A multiple primary endpoint is chosen:
 
First endpoint: Intraoperatively required amount of HES (10%, 6%) (ml)
 
Second endpoint: Time until fully on oral (solid) diet (days)
                                                                                                                                                                                                                                                                                                                                                                                                                                                                                                                                                                                                                                                                                                                                                                                                                                                                                                                                                                                                                                                                                                                                                                                                                                                                                                                                                                                                                                                                                                                                                                                                                                                                                                                                                                                                                                                           |

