|                               | 
<math>\alpha</math>1-MG, <math>\beta</math>-NAG, creatinine
 
 
o postoperative days 3 and 7: creatinine in serum
 
 
day +2 – day +15 maximal (i. e. as long as patient receives parenteral/enteral nutrition) on respective care unit (control on subsequent day for predecessor day)
 
 
▪ control of nutrition/diet: Is parenteral nutrition administered – Has the patient taken nutrients orally at least for three times that day.
 
 
3 months after surgery
 
 
▪ Health Related Quality of Life (HRQoL)
 
                                                                                                                                                                                                                                                                            |
| Duration of Study per Patient | 
Start of study: with randomisation
 
Treatment period (infusion of Investigational Products):
 
During surgery (guided by measurement of oesophageal Doppler)
 
End of study: Postoperative Day 15 or discharge from hospital whatever occurs first
 
Last evaluation of certain parameters will be 3 months post-surgery respectively when DRG data are available
                                                                                                                                                                                                                                                                                                                                                                                                                                                                                                                                                       |

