#### **7.1.1 Primary Variable**

A multiple primary endpoint is defined which is “the intra-operative amount (in mLs) of colloidal volume replacement therapy during target directed volume replacement therapy” as the first primary endpoint and “days until fully on oral (solid) diet” as the second primary endpoint (full on oral diet is defined by the absence of parenteral and enteral nutrition and the patient is able to take oral nutrition for at least three times that day).

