### Other

Aldrete Score (refer to in Marshall et al. 1999, appendix 8): on admission to ICU and once daily on ICU.

Length of stay in ICU/IMCU (fulfillment of discharge criteria) – assessment will be done once daily (evening) on ICU. If fit-for discharge criteria are not yet fulfilled at POD 5 it will be continued to check until fulfillment or until study end, whatever occurs first.

Morbidity and complication rate: surgical complications such as re-do surgery (e. g. anastomotic insufficiency or bowel leakage), disturbed wound-healing or medical complications which delay time to fully oral nutrition will be assessed and documented at study end

Combined outcome parameter of prolonged length of stay (based on mean length of stay according to the German Diagnosis Related Group System D-DRG) or death.

Health Related Quality of Life (HRQoL) before and 3 months after surgery (EQ-5D, the EuroQol Group, <http://www.euroqol.org>)

**NOTE:** measurements on ICU (if not otherwise mentioned) will be performed until “fit for discharge criteria are fulfilled or until day +5 (incl. day +5) whatever occurs first.

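### The second primary endpoint is called full oral (solid) diet, but no criterion asks about solid food, its definitions conflict, and nutrition recording can stop before the endpoint is met

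*Protocol*

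**What the plan says.** The synopsis lists "Second endpoint: Time until fully on oral (solid) diet (days", and sections 7.1.1, 8, 12.1 and 16.1 also carry the word *solid* in the name. Sections 11 and 16.3 name the same variable without it.

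The criterion in section 12.1 has two parts. First, "Fully on oral (solid) diet is reached when no more parenteral and enteral nutrition is given". Second, "the patient has taken nutrients via the oral pathway for at least three times that day". Section 7.1.1 has the same two parts, "full on oral diet is defined by the absence of parenteral and enteral nutrition", but words the second as "the patient is able to take oral nutrition for at least three times that day".

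Data come from a daily check, made on the following day, for at most 15 days. The synopsis asks whether parenteral nutrition is given and "Has the patient taken nutrients orally at least for three times that day". Section 11 ends the check once the patient is off parenteral nutrition and has had oral intake "at least three times that day no further recording of nutritional diet is required". Section 14.1 has a matching stop rule, again naming only parenteral nutrition.

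Section 12.3 expects events that could interrupt feeding (re-do surgery, anastomotic or bowel leakage) and adds that "medical complications which delay time to fully oral nutrition will be assessed and documented at study end".

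**The concern.** This endpoint is tested confirmatorily at the full 5% once the first is significant, and it is the only recovery outcome of the two primaries. A positive result would naturally be reported under its name, as earlier return to solid diet. What the protocol fixes for collection is the first day with three oral intakes of any kind off artificial nutrition. If food consistency and later feeding days are not recorded, an analysis plan cannot reliably restore them. Centres could also date the endpoint differently, depending on whether they judge ability or actual intake, and on whether tube feeding holds the check open.

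**Working it through.** This is a matter of definition, so the passages are compared first.

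| Place | Solid intake required? | Ability or intake | Artificial nutrition named |
|---|---|---|---|
| 7.1.1, definition | No (name only) | able to take | parenteral and enteral |
| 12.1, definition | No (name only) | has taken | parenteral and enteral |
| Synopsis, daily question | No | has taken | parenteral in the question; both in the line saying how long the check lasts |
| 11, stop rule | No | has taken | parenteral only |
| 14.1, stop rule | No | able to take | parenteral only |

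Three hypothetical patients show the consequences.

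1. *Liquids.* A patient off parenteral and enteral nutrition takes three liquid supplements on day 6. Section 12.1 is met, so the value is 6 days until full solid diet, although no solid food was eaten.
2. *Tube feeding continues.* A patient off parenteral nutrition, still tube-fed, takes oral nutrients three times on day 6. The stop rules in 11 and 14.1 are met, but 7.1.1 and 12.1 are not. The stop rules' remark that the oral route is not the enteral one limits which intakes count; it does not require tube feeding to have ended. Recording may stop before the defined day. The synopsis, which continues the check while either form is given, points the other way.
3. *Relapse.* A patient qualifies on day 6 and returns to parenteral feeding on day 8 after a leak. The value stays 6, and the nutrition check has already ended.

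Next, the plan's own figures for this endpoint (section 16.4): difference 1.5 days, effect size 0.698, two-sided 5%, Mann-Whitney test.

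- Implied SD = 1.5 / 0.698 = 2.15 days.
- Noether's formula: n per group = (z₀.₉₇₅ + z_power)² / [6(p − 0.5)²], with p = Φ(0.698/√2) = 0.689.
- For 80% power: (1.960 + 0.842)² / (6 × 0.1892²) = 7.849 / 0.2148 = 36.5, so 37 per group, as stated.
- Power with 69 per group: Φ(√(6 × 69 × 0.1892²) − 1.960) = Φ(1.89) = 97.1%, against 97% stated.

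The protocol's figures reproduce.

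For the size of the effect, the protocol gives no liquid-diet or relapse rate. If a fraction f of an arm is dated s days too early, that arm's mean falls by f × s, and the difference between arms moves by (f₁ − f₂) × s. On assumed values only:

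- Liquids, f = 10%, s = 1 to 2 days: 0.1 to 0.2 day in that arm, or 7% to 13% of 1.5 days.
- Relapse, f = 10%, s = 5 to 7 days: 0.5 to 0.7 day in that arm, or 33% to 47% of 1.5 days.
- With f and s equal in both arms, the mean difference moves by zero in either case. With relapse rates 5 points apart it moves by 0.05 × 5 to 0.05 × 7 = 0.25 to 0.35 day.

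The planned test works on ranks, so these mean shifts are only a guide.

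**The case against.** The strongest reply is that time to first attainment is a legitimate endpoint, judged by the same rule in two blinded HES arms, and that the hypothesis in section 16.3 concerns full oral diet without the word *solid*. On that view the fault lies in the label. Much of this stands. A reader might infer that the primary must be a sustained, relapse-free diet. The protocol does not support that: first attainment is a defensible choice, and a stricter rule could leave more patients without a value by day 15, while section 16.5 rules out imputation.

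Three other stronger readings also fail.

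- *Three oral intakes alone suffice.* They do not; sections 7.1.1 and 12.1 also require parenteral and enteral nutrition to have ended.
- *Relapses leave no trace in the data.* This is not established. The schedule in 14.2 lists parenteral nutrition to day 15 under concomitant medication, section 11 says management of enteral nutrition is documented in the CRF, and complications are documented at study end. The CRF is not at hand. What can be said is that the nutrition check stops, and that no passage requires a return to artificial feeding to be dated for this endpoint.
- *The comparison is biased by a third to a half of the target difference.* That figure is a one-arm shift on assumed rates.

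The wording in 12.1 that no more artificial nutrition is given could be read as permanent cessation. With the check stopped at the first qualifying day, that reading cannot be applied reliably.

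**Conclusion.** The point holds as a defect of definition and recording. *Solid* is in the endpoint's name in five places and in none of the criteria or daily questions. Ability and actual intake are used interchangeably. The stop rules leave out enteral nutrition, which the definition requires to have ended, so recording can close early. A later return to artificial feeding falls outside the nutrition check.

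The size of any effect cannot be computed from the protocol. Bias between arms would need liquid-only, tube-fed or relapsing cases to differ by arm, and nothing in the protocol shows that they would. The sample size and power statements are not affected as arithmetic. What the data cannot support as planned is a conclusion worded as time to full *solid* diet.

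**What to change.** Use one definition in the synopsis and in sections 7.1.1, 11, 12.1 and 14.1: *solid food taken by mouth on at least three occasions that day, with neither parenteral nor enteral nutrition given*. Alternatively, delete *(solid)* from the endpoint name and from any conclusion, while still settling on actual intake and on both feeding routes.

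Make the daily check ask separately about parenteral nutrition, enteral nutrition and, if *solid* is kept, solid intake. Continue it to day 15 or discharge, whichever comes first, instead of stopping at the first qualifying day. Keep first attainment as the primary definition, and report the first qualifying day without later return to parenteral or enteral nutrition as a supportive analysis.

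The cost is a few more days of a bedside question already scheduled to day 15. If solid intake is required, the endpoint falls slightly later, and a few more patients may not reach it by day 15. It may also differ from the definition behind the hospital data that gave the 0.698 effect size, so that assumption should be checked again at the planned blinded variance review.
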